## Abstract

**Background/Objectives:** Fear of falling (FOF) and falls are prevalent issues among older adults, leading to activity restriction, decreased quality of life, and increased dependency. This study aims to assess the effectiveness of a nurse-led health education intervention to reduce FOF and fall incidence in older adults within primary care settings. **Methods:** This two-arm, multicenter, parallel, cluster-randomized clinical trial includes ten primary care centers in Spain and will enroll 150 adults over 65 years with FOF, mild or no functional dependence, and independent ambulation. Participants will be randomized to either the intervention group, which will receive five initial group education sessions led by community nurses and a booster session at six months, or the control group, which will receive usual care. Primary outcomes include FOF, assessed using the Short Falls Efficacy Scale-International (FES-I), and fall incidence. Data collection will occur at baseline, one month, six months, and twelve months post intervention. This study has been approved by the Ethics Committee for Research with Medicinal Products at Gregorio Marañón University Hospital in accordance with the Declaration of Helsinki. **Expected Outcomes:** The health education intervention is expected to significantly reduce both FOF and fall incidence, supporting the integration of FOF management in routine primary care for older adults, with potential benefits for safety and quality of life. Trial Registration: ClinicalTrials.gov: NCT05889910. The study protocol follows CONSORT and SPIRIT guidelines.

## 1. Introduction

Fear of falling (FOF) is a persistent concern about falling that causes individuals to avoid activities that they are still capable of doing [1]. In the long term, this problem increases the risk of falls [2], impairs functional ability in older people, [3,4] and even increases the risk of frailty, dependence, and death, affecting those most concerned about falls physically, socially, and psychologically [5,6,7].

FOF is common among community-dwelling older people, with its prevalence ranging from 26.9% to 49.4% worldwide [3,8,9]. Risk factors for FOF are manifold, including old age, being female, living alone, experiencing depression or anxiety, prior falls (especially those resulting in injuries, fractures and/or hospitalization), gait and balance disorders, chronic pain, pharmacological treatments (anxiolytics and antidepressants), and sensory deficits [10,11,12].

Moreover, according to the World Health Organization’s Global Burden of Disease report, fall-related injuries are the third leading cause of years lived with disability [13]. The prevalence of falls in people over 65 years of age is high. Approximately 30% have fallen once and more than 15% have fallen at least twice [14]. The annual incidence of falls ranges between 30% and 40% in those over 65 years of age and up to 50% in those over 80 years of age [15].

Risk factors associated with falls are also multiple, including being female, advanced age (over 80 years), unsuitable environmental factors, decreased ability to perform basic or instrumental activities of daily living, decreased functional ability (as an indicator of frailty), sensory deficit, comorbidities, polypharmacy, urinary incontinence, depression, low weight, and low income [2,10].

Traditionally, FOF has been considered as a ‘post fall syndrome’; however, studies have shown that, although concern about falling is more common in those who have experienced a fall, it can occur in individuals who have never fallen and should therefore be considered as an independent risk factor in the development of disability in older people [3].

Evidence on the management of FOF indicates that there are effective interventions to reduce FOF and overcome activity restrictions that can lead to disability in the field of primary care. The interventions that have been shown to be most effective are based on cognitive behavioral therapy programs combining multicomponent exercise, i.e., balance, gait speed, and lower limb strength training [16,17,18]. Other interventions that have been shown to be effective include tai chi [17], vitamin D supplementation, whole-body vibration therapy, and guided relaxation [19]. In addition, evidence on reducing the incidence of falls in community-dwelling older people suggests that fall prevention education programs and multicomponent exercise programs are the most effective interventions [20,21,22,23,24].

On the other hand, it is important to note that the use of nursing methodology to improve patient health outcomes is under development. According to Alfaro-Lefevre, the nursing care process is defined as a systematic and organized method of delivering personalized nursing care when responding to an actual or potential health disturbance, consistent with the basic approach of addressing the needs of each individual or group of individuals [25]. Several studies have identified that patients assigned to nurses who systematically and continuously use nursing methodology achieve better health outcomes [26,27]. The advantages of using this methodology include comprehensive patient care and reduced variability in the care provided by different professionals, which, in turn, facilitates the continuity of care [25]. Significant improvements have been documented in patients whose nurses use the nursing process in their routine clinical practice for intermediate outcomes, such as increased coverage in cervical cancer screening programs, increased vaccination coverage (rubella, tetanus, hepatitis B), glycemic control in patients with diabetes, perceived control of anxiety, and increased knowledge of chronic obstructive pulmonary disease [27,28,29,30]. Regarding the FOF and falls in older people in particular, according to Domínguez-Fernández’s doctoral thesis, published in 2021 [26], the regular use of nursing methodology (the application of care plans) improves the FES-I scale scores as well as the incidence of falls in people over 75 years of age compared to nurses who do not use it.

Primary care professionals play a key role in the early identification and treatment of FOF and falls in community-dwelling older people [8].

Therefore, given that (a) FOF and falls are interconnected, (b) they are highly prevalent problems, and (c) several studies show that it is possible to reduce concerns surrounding FOF and prevent falls by following intervention programs in people living in the community, we believe it is desirable to design and apply a standardized care plan that can be implemented in primary care facilities (PCFs) in a systematic way to address these problems in an ongoing and programmed manner, focusing on cognitive behavioral therapy, multicomponent exercise, and fall prevention.

## 2. Experimental Design

### 2.1. Aims

#### 2.1.1. Primary Objective

To assess the effectiveness of implementing a health education intervention to reduce FOF in community-dwelling individuals over 65 years of age.

#### 2.1.2. Secondary Objectives

To assess the effectiveness of implementing a health education intervention to reduce falls in community-dwelling individuals over 65 years of age.To analyze the relationships between patients’ sociodemographic, clinical, and functional variables and each of the following: the FES-I short questionnaire scores and the incidence of falls in both the control and intervention groups.To analyze the effect of a health education intervention on functional variables, emotional state, ability to practice self-care, and perceived health.

### 2.2. Research Hypothesis

Implementation of a standardized nursing care plan for at least six weeks reduces FOF (defined as patients’ confidence in being able to perform activities of daily living without losing balance or falling, as measured by the short FES-I scale) by at least 3.8 points among independent community-dwelling individuals over 65 years of age at six and 12 months post intervention compared to usual clinical nursing practice in these patients.

### 2.3. Design

The CONSORT (Consolidated Standards of Reporting Trials) and SPIRIT (Standard Protocol Items: Recommendations for Interventional Trials) guidelines were used to design this study. This is a parallel group, multicenter, open, two-arm, superiority cluster-randomized clinical trial with a 1:1 allocation ratio.

The PCFs participating in this study are randomly assigned to either the intervention or control arm. Participants randomized to the intervention group will receive a group-based health educational intervention based on the proposed protocol. Participants in the control group PCFs will receive care as usual.

### 2.4. Setting of This Study

This study will be carried out at ten PCFs in Madrid, Spain.

### 2.5. Recruitment of Facilities and Professionals

For recruitment purposes, researchers will contact PCFs and clinicians via an email sent by a scientific society of primary care nurses. Professionals interested in participating will be interviewed by the principal investigator.

Participating facilities shall have at least three nurse collaborators who will be able to deliver the proposed health educational intervention, as well as a suitable room available in the same basic healthcare district in which to implement the intervention in case they are assigned to the intervention group.

Participating professionals will become members of the FEARFALL_CARE Clinical Care Group. Each nurse will be recruiting approximately five participants. If a PCF is assigned to the control group, professionals will perform recruitment, study assessment interviews, and clinical practice as usual. If a PCF is assigned to the intervention group, at least three nurses shall participate in the recruitment and assessment interviews and at least two nurses will implement the educational group intervention (with one delivering the session and the other acting as an observer).

Finally, to minimize the risk of selection bias, PCF professionals shall recruit participants without the knowledge of the group to which they will be assigned.

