### 2.9. Study Blinding

The intervention can only be blinded during participant recruitment, when the professionals in the Clinical Care Group will not know to which group they will be assigned. To avoid interpretation bias throughout the statistical analysis, patient information will be encoded. The data analysis will be performed by a third party not involved in the fieldwork. The principal investigator will assess the results and participate in the fieldwork at one PCF, which means that she cannot be blinded when assessing the results obtained.

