### Limitations

This study features a number of drawbacks. Firstly, a selection bias may be introduced during recruitment at PCFs. The recruitment of participants who are visiting their healthcare professionals could influence the results. However, it is not possible to recruit them randomly using databases, as there are no registers of patients with FOF. Secondly, given the nature of this study, the health education intervention cannot be blinded to participants. Thirdly, the validity of the data to be extracted from health records could be underestimated in cases with poor documentation. Finally, participants will be recruited only in the Autonomous Community of Madrid due to financial and human resources constraints, which may limit the generalizability of the results.

Difficulties may also be encountered when implementing this study, as it is an health education interventional trial with four scheduled visits, in which attrition rates may be high due to dropouts, non-attendance, or non-compliance with instructions. To mitigate this problem, we aim to maximize patient retention through regular telephone calls, in which appointments will be arranged with participants prior to each interview. Furthermore, an additional 20% of participants will be recruited to accommodate for potential losses.

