## Figures and Tables

**Figure 1 healthcare-12-02510-f001:**
[figure not shown]
CONSORT flowchart of participants.

**Table 1 healthcare-12-02510-t001:** Short FES-I scale.

Short FES-I Scale How Concerned Are You About the Possibility of Falling While…?	Not at All Concerned	Somewhat Concerned	Fairly Concerned	Very Concerned
1. Getting dressed or undressed	1 □	2 □	3 □	4 □
2. Taking a bath or shower	1 □	2 □	3 □	4 □
3. Getting in or out of a chair	1 □	2 □	3 □	4 □
4. Going up or down stairs	1 □	2 □	3 □	4 □
5. Reaching for something above your head or on the ground	1 □	2 □	3 □	4 □
6. Walking up or down a slope	1 □	2 □	3 □	4 □
7. Going out to a social event (e.g., religious service, family gathering or club meeting)	1 □	2 □	3 □	4 □
SUBTOTAL:	Add all the 1’s	Add all the 2’s	Add all the 3’s	Add all the 4’s
	Short FES-I ≥ 11: Fear of falling			

**Table 2 healthcare-12-02510-t002:** Summary of visits and variables.

Variables	Visits						
	Initial Visit. Screening	Pre-Intervention Baseline visit ^1^	Five Initial Group Sessions	Visit Post Initial Intervention ^2^	Visit at Six Months Post Initial Intervention ^3^	Booster Session	Visit at 12 Months ^4^
Review of eligibility criteria	x						
Informed consent	x	x					
Primary outcome variable: Short FES-I		x		x	x		x
Secondary outcome variable: Post intervention falls		x		x	x		x
EXPLANATORY VARIABLES							
Sociodemographic variables		x					
Functional variables		x			x		
Usual footwear		x			x		
Clinical variables		x					
Falls during intervention				x		x	
Ability to practice self-care		x		x	x		x
Perceived health and anxiety		x		x	x		x
Acceptability (among patients)				x			

^1^ ±2 weeks before the health education intervention (for the intervention group: (IG)). ^2^ ±2 weeks after the initial sessions (IG). ±4–8 weeks after randomization (for the control group (CG)). ^3^ ±2–4 weeks, at six months after randomization (CG) or after the initial health education intervention (IG), always prior to the booster session. ^4^ ±2–4 weeks, at 12 months post randomization (CG), at six months after the booster session (IG).

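### At an intervention facility with the minimum three nurses, the two session nurses are also outcome assessors, and nothing keeps them from collecting the self-rated follow-up outcomes in this open trial

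*Protocol article*

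**What the plan says.** Section 2.3 describes the design: "This is a parallel group, multicenter, open, two-arm, superiority cluster-randomized clinical trial with a 1:1 allocation ratio".

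Section 2.5 sets the staffing. "Participating facilities shall have at least three nurse collaborators who will be able to deliver the proposed health educational intervention". At an intervention facility "at least three nurses shall participate in the recruitment and assessment interviews and at least two nurses will implement the educational group intervention"; the two implementing nurses split the work, "with one delivering the session and the other acting as an observer". At a control facility "professionals will perform recruitment, study assessment interviews, and clinical practice as usual". Section 2.7 plans about 15 patients per facility and about five per nurse, which implies three nurses.

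The primary outcome (Section 2.11.1, Table 1) is the seven-item short FES-I, in which participants rate their own worry; the question begins "How Concerned Are You About the Possibility of Falling". It is collected at baseline and at 1, 6 and 12 months. Falls come from the medical record or the patient's report (Section 4.4).

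On blinding, Section 2.9 states: "The intervention can only be blinded during participant recruitment". It adds coded data and an analyst from outside the fieldwork. The Limitations section concedes that "the health education intervention cannot be blinded to participants" and says nothing about who assesses the outcomes.

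**The concern.** At a three-nurse intervention facility, the nurses who lead and observe the course are also assessors of whether it worked. A participant asked by the course leader how worried they still are about falling has a reason to give an encouraging answer. The same holds for reporting a fall. If that pull is stronger in the intervention arm than in the control arm, the difference goes straight into the estimated effect, in the direction of the hypothesis. More patients or more facilities would not shrink it, and the planned comparison of groups cannot separate it from a real effect. Coding the data and using an outside analyst protect the analysis, not the collection. Common training makes collection uniform but does not separate the person who delivers from the person who assesses.

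**Working it through.** **1. Do the roles have to overlap?** Section 2.5 gives at least 3 assessors and at least 2 implementers. With k nurses at a facility, the smallest number holding both roles is max(0, 3 + 2 − k):
- k = 3: 2 nurses, so both session nurses are assessors
- k = 4: 1 nurse
- k = 5: 0 nurses

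At the minimum staffing, which is also the staffing implied by 15 patients at five per nurse, the rule puts both session nurses among the assessors. It does not say which visits each nurse takes, and nothing excludes session nurses from the follow-up visits.

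**2. The plan's own sample size** (Section 2.7: difference 3.8, SD 5.1, ICC 0.1, alpha 0.05, power 80%, 12 per centre, 5 centres per arm, 20% loss).
- Without clustering: 2 × (5.1 × (1.960 + 0.842) / 3.8)² = 28.28 per arm
- Design effect: 1 + (12 − 1) × 0.1 = 2.1
- 28.28 × 2.1 = 59.4, so 60 per arm and 120 in total; 120 / 0.8 = 150

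The stated 120 and 150 reproduce with a two-sided test.

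**3. How sensitive would the result be?** The standard error of the difference is 5.1 × √(2 × 2.1 / 60) = 1.349 points. The documents give no size for assessor bias, so the shifts below are assumptions. The table gives the two-sided 5% rejection rate when there is no true effect.

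| Assumed net shift between arms | Share of 3.8 | t test, 8 df (10 facilities − 2) | Normal test |
|---|---|---|---|
| 0.5 | 13% | 6.2% | 6.6% |
| 1.0 | 26% | 10.1% | 11.5% |
| 1.5 | 39% | 16.6% | 19.9% |
| 2.0 | 53% | 25.8% | 31.7% |

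Neither column is the planned test, which is a fixed-effects ANOVA with facility nested in group (Section 4.4).

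**4. Workload of separating the roles.** Section 4.3 gives follow-up visits of 25 + 45 + 20 = 90 minutes. For 15 patients this is 15 × 90 = 1,350 minutes, or 22.5 hours per facility over the year. Shared by three nurses it is 7.5 hours each. The total does not change.

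**The case against.** - **Mode of completion.** The article does not say that the short FES-I is read out. Section 2.5 speaks of assessment interviews, but Section 2.11 refers to Supplementary File S1 for the tools, and Table 1 is a tick-box form. A reader might infer that participants voice their answers to the course leader; the documents do not establish this. If S1 provides for self-completion, part of the remedy is already there. Who collects patient-reported falls, and when the form is filled in, would still matter.
- **Both arms.** A reader might infer that the pull exists in the intervention arm only. Section 4.2 does not support that: control nurses give structured education, including exercise and fall prevention, to patients in stated SPPB and Barthel bands, and Section 2.5 has control professionals do the assessments too. This stands. The bias is the difference between arms, which may be smaller than a one-arm argument suggests.
- **The third nurse is not blind.** That nurse works at the facility, knows its allocation and will have recruited some of the patients. In the control arm, patients would still be assessed by nurses who treat and educate them, so separation alone leaves an asymmetry. This also stands, and is why self-completion in both arms comes first in the remedy.
- **Conflict with the staffing rule.** At a three-nurse facility, keeping session nurses out of follow-up contradicts the three-assessor rule unless that rule is narrowed. True; the remedy has to say so.
- **Disclosure.** The open design, the limits of blinding and the unblinded participants are all stated. The overlap between delivering and assessing is not.
- **Principal investigator.** Section 2.9 says that the principal investigator does fieldwork at one facility. It does not say that this includes outcome collection, or in which arm, so only a conditional rule is justified.

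**Conclusion.** The point holds in a limited form. The staffing rule makes both session nurses assessors at a three-nurse intervention facility, and the article contains no rule that keeps them from collecting the short FES-I and patient-reported falls at follow-up. With a self-rated primary outcome in an open trial, this is an avoidable source of detection bias.

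Its size is unknown. It would be tempting to read the table as saying that the false-positive rate is 10% or 26%, or that the remedy removes that much. Neither follows. The shifts are assumed, they stand for a net difference between arms, and bias from participants who know their own arm would remain afterwards. The figures show only that a shift of one point, about a quarter of the target difference, would matter at this standard error.

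The conclusion assumes staffing at or near the minimum. With four nurses at least one overlap is still forced; with five the roles can be separate, but the text does not require it. The sample size is unaffected.

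**What to change.** 1. State that in both arms and at every visit, baseline included, participants complete the short FES-I themselves on paper before contact with the nurse, with any reading help from someone who did not deliver the sessions. If Supplementary File S1 already provides for self-completion, only the timing needs adding. Other questionnaires can stay with the nurse, so the health monitoring in Section 4.6 is not affected.
2. In Section 2.5, limit the three-assessor rule to recruitment and baseline. At intervention facilities, have a nurse who neither led nor observed the sessions collect the 1-, 6- and 12-month outcomes. At the six-month visit, place the review of issues raised in the intervention after outcome collection.
3. If the principal investigator's fieldwork includes outcome collection, apply the same separation there.
4. Add to the limitations that outcome assessors are unblinded.

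**Cost.** Protocol wording and a reallocation of work, with no added staff. At a three-nurse intervention facility, one nurse carries about 22.5 hours of follow-up instead of 7.5, with less cover for absence in a trial that already expects attrition. The changes reduce detection bias; they do not blind the assessors or remove it.

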### 2.6. Study Population

The study population will be individuals over 65 years of age who meet the eligibility criteria:

#### 2.6.1. Inclusion Criteria

Individuals over 65 years of age on the start date of this study.Individuals who are independent for activities of daily living or with mild functional dependence (Barthel Index score ≥ 60 and Short Physical Performance Battery (SPPB) ≥ 4).Independent for ambulation (can walk 45 m unaided or with a cane).Without cognitive impairment (Mini-Mental State Examination (MMSE) ≥ 24).With FOF (short FES-I ≥ 11).

#### 2.6.2. Exclusion Criteria

People with the following medical diagnoses or health conditions (coded according to the International Classification of Diseases (ICD–10):-Diagnosis of mental, behavioral, or neurodevelopmental disorders: delirium, dementia, amnestic disorders, or other cognitive disorders (F05.0; F05.9; F00; F02.8; F03; F04; R41.3; F06.9). Mental disorders caused by a general medical condition, not elsewhere classified (F06.1; F07.0; F09). Schizophrenia or other psychotic disorders (F20; F22; F23; F24; F29).-Diagnosis of neurodegenerative diseases: Parkinson’s disease (G20); Alzheimer’s disease (G30); multiple sclerosis (G35); myasthenia gravis, or other myoneuronal disorders (G70).-Diagnosis of blindness or low vision (H54).-Diagnosis of conductive or sensorineural hearing loss, bilateral or uncorrected with a hearing aid (H90.0; H90.2; H90.5; H90.6; H90.8) or other types of hearing loss (H83.3; H91), as long as it impairs participants’ understanding.-Diagnosis of acute ischemic heart diseases and cerebrovascular diseases in the previous year (I20–I24; I60–I63; I67; I68).-Other diseases of the circulatory system that contraindicate the multicomponent physical exercise program [31]: other forms of heart disease (I30–I52) (e.g., uncontrolled atrial or ventricular arrhythmias, dissecting aortic aneurysm, severe aortic stenosis, acute endocarditis/pericarditis, uncontrolled arterial hypertension, acute thromboembolic disease, severe acute heart failure, severe acute respiratory failure, uncontrolled orthostatic hypotension; diabetes mellitus with acute decompensation or uncontrolled hypoglycemia (E10-E14), recent fracture in the last month (T14.2) (for strength training) or any other circumstance that the professional considers prevents this type of patients from performing physical activity in the program.Hospitalization during the recruitment period or expected admissions during the study period.Institutionalized patients or with frequent changes in address.

